#### Exploratory analyses

Exploratory analyses seek to address the concern that the number of peers assigned to a peer coach may impact their ability to successfully coach individuals with T2D and may have a potentially deleterious impact on their own T2D self-care. This hypothesis will again be tested using longitudinal linear mixed models. HbA1c levels over time (for both peers and peer coaches) will be modeled as a function of the number of concurrent peers a peer coach has. This will help inform future studies of the ideal number of peers a peer coach has at any given time.

#### Assessing implementation

For all PRISM-guided interviews, two members of the research team with academic training and pragmatic experience in implementation science as well as substantial qualitative research experience will independently code the data and map responses to relevant PRISM domains, as outlined in previous applications of PRISM [34]. Should coding conflicts arise, a skilled implementation scientist with ample research using PRISM/RE-AIM will mediate and help build coding consensus. Data from midpoint iterative RE-AIM planning will be used primarily as quality improvement and will be presented to members of the implementation and research teams using descriptive statistics, graphs, charts, and de-identified thematic analysis of any explanatory feedback. Finally, for the 12-item feasibility, acceptability and appropriateness survey, scores for each of the three scales will be summed and averaged, with higher scores indicating more favorable implementation outcomes. These data will provide added context to which factorial condition was perceived by both implementers and participants as most favorable. Collectively, these data will identify necessary implementation strategies, as well as facilitators and barriers to implementation, to guide future scale-up and scale-out activities throughout rural Appalachia.

## Discussion

Peer health coaching is an approach that relies on social relationships and has resulted in improved outcomes in participants with T2D. In studies of predominantly low-income and minority populations, peer health coaches have been shown to help improve medication adherence and blood glucose monitoring [55–61]. Peer health coaches are usually individuals who have successfully coped with a similar condition as their peer [28]. In peer health coaching interventions, coaches receive training focused on communication skills, including empathetic listening, helping peers clarify life goals, and problem solving with the aim of having the coach support their peer [62]. For the current study, we have chosen a peer coach EBI that showed an HbA1c reduction of 1.07% among peer participants [63].

We acknowledge the following potential challenges with this proposal. First, we may encounter challenges with recruitment and retainment of older adults in rural communities; however, we involved key stakeholders in the development of this study and have included their recommendations in our recruitment efforts along with previously successful recruitment strategies. Second, we acknowledge that older adults may find the use of REDCap links to complete data collection at baseline, 6 months (end of intervention), and 3- and 6-months post-intervention challenging; however, these potential challenges are integral to the evaluation and implementation of the intervention. Lastly, we recognize the lack of a usual care arm may be considered a weakness of our study design and/or a challenge to the interpretation of our findings. Still, we opted not to have a usual care arm because of the dire circumstances of those diagnosed with T2D living in Appalachia Kentucky (e.g., high prevalence, disease severity, lack of resources). In addition, the goal of this pilot and feasibility study is to identify efficacious components to refine a peer support EBI targeting older adults in rural Appalachia. The factorial design provides the scientific rigor to accomplish this goal without the use of a control or usual care group.

The findings from this study will be used to test the effectiveness of the refined intervention in a larger, adequately powered study. Data collected on implementation science components, feasibility, and acceptability will be used to scale up the peer health coach intervention. Lastly, the subsequent study will assess the healthcare utilization/cost effectiveness component of the Main Effects of Social Support Model of the large-scale intervention (e.g., economic evaluation of cost, implementation specific cost assessment) as well as considerations for sustainability. In conclusion, by delivering a tailored, evidence-based peer support intervention (i.e., peer health coaching), we will gain valuable insight in how to leverage existing social cohesion and social support within rural Appalachian Kentucky to promote healthy behaviors and improve T2D related clinical outcomes.

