**Method:**

To address this gap, we conducted formative research with stakeholders, and collaboratively identified an acceptable and feasible peer support EBI—peer health coaching (PHC)—that has resulted in improved clinical and psychosocial T2D-related outcomes among participants who did not reside in rural communities nor were ≥65 years. The goal of the proposed study is to use a 2x2 factorial design to test the adapted PHC components and determine their preliminary effectiveness to promote self-care behaviors and improve glycemic control among older adults living in Appalachian Kentucky. Testing the PHC components of the peer support intervention will be instrumental in promoting care for older adults in Appalachia, as it will allow for a larger scale intervention, which if effective, could be disseminated to community partners in Appalachia.

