#### 1. Use a 2x2 factorial design to determine which EBI components are associated with improved T2D-related outcomes in older adults living in Appalachia Kentucky

The independent variables for the factorial design are (1) how the peer coach is selected (self-selected by participant vs matched) and (2) frequency of contact (once per week vs every 2 weeks). We will evaluate effectiveness of each group using hemoglobin A1c (HbA1c) as the primary outcome while also evaluating self-care activities and T2D-related psychosocial factors as secondary outcomes

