### Peer participant eligibility criteria

Eligibility criteria for peer participants include:

confirmed diagnosis of T2D via point-of-care HbA1c assessment;residence in Appalachia Kentucky;HbA1c ≥ 7.5% in the previous 6 months;age ≥ 55 years.

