#### Random assignment of peer participants to intervention condition

Participants will be consented, enrolled and randomized into one of four groups. During the consenting process, it will be explained that participants can withdraw at any time. Participant can be randomized into one of the following groups: (1) self-select mentor, once per week contact; (2) self-select mentor, every two weeks contact; (3) matched with mentor, once per week contact; or (4) matched with mentor, every two weeks contact. For participants who are randomized into a group where they are matched with a peer health coach, matching areas include similarity of life stage (e.g., age), county of residence, and duration of disease diagnosis. However, the primary matching area for this study will be county of residence. This decision was informed by key informants who highlighted that Appalachians’ sense of identity is closely linked with the county in which they reside and that there will be an additional level of trust and comfort (or lack thereof) based on where their peer resides. For participants who are randomized into the group where they are able to self-select their peer coach, they will be provided with profiles of eligible coaches. These profiles will include age, sex, marital status, where they reside (county and town), duration of diabetes diagnosis, current HbA1c, and hobbies. Peer participants will be able to rank their top three coaches. The study team will try to match participants with their preferred coach. However, once a coach has been assigned three peer participants, they will be removed from the pool of coaches to choose from.

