## Data analyses

### Descriptive analysis

Descriptive data in the form of means (standard deviations) for interval-level variables and frequencies (percentages) for qualitative variables will be presented for the entire population and by trial arm. Prior to conducting and interpreting the main analyses, the distribution of all outcome variables will be examined to ensure the tenability of parametric assumptions.

### Analytic plan for aim 1

The repeated measures, factorial design will be analyzed using longitudinal linear mixed models. Linear mixed effects models are an extension of the general linear model and are suitable when the independence of observations assumption is violated, which occurs in this study when individuals are measured repeatedly over time. Additionally, these models have the benefit over a repeated measures ANOVA of utilizing all data from participants who were measured on some, but not necessarily all of the measurement occasions. The main outcome for this aim is HbA1c levels at the first post-intervention measurement occasion. Fixed effects of interest will include measurement occasion, peer support type, and contact frequency. Preliminary models will include all two-way interactions, and non-significant higher-order interactions will be removed to arrive at the most parsimonious model. The model will incorporate random effects to account for repeated measures on individuals using an autoregressive covariance matrix. Due to randomization, we do not anticipate any differences in covariates between groups; however, we will evaluate differences by main effects and adjust for them if necessary. Additional analyses related to Aim 1 will look at between-group differences in psychosocial factors over time.

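### Every group is coached, so the trial can show which level of each component is better, but not that coaching, any group or any component works against no coaching, as parts of the article claim

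*Protocol article*

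**What the plan says.** Study aims, item 1, defines the two factors as "how the peer coach is selected (self-selected by participant vs matched) and (2) frequency of contact (once per week vs every 2 weeks". The section on random assignment lists four groups, each with a coach, and the intervention section gives every participant six months of contact with that coach.

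Several statements go beyond a comparison of levels. Study aims, item 1: "We will evaluate effectiveness of each group using hemoglobin A1c (HbA1c) as the primary outcome". The Abstract says the components will be tested to "determine their preliminary effectiveness to promote self-care behaviors and improve glycemic control". The Discussion gives the goal as identifying efficacious components. It grants that the lack of a usual-care arm may be seen as a weakness or may complicate interpretation, and then closes the matter with: "The factorial design provides the scientific rigor to accomplish this goal without the use of a control or usual care group".

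The analytic plan for aim 1 takes HbA1c at the first post-intervention occasion as the main outcome and says: "Fixed effects of interest will include measurement occasion, peer support type, and contact frequency". Participants qualify with "HbA1c ≥ 7.5% in the previous 6 months".

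**The concern.** A factorial trial can do without a separate control group, and still speak about the absolute effect of a component, when one level of each factor is the absence of that component. Neither factor here has such a level. The design therefore lacks the property that the last sentence of the limitations paragraph gives it.

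Two misreadings are at stake. If the two levels of a factor give similar HbA1c, the result could be reported as both working, when the data fit equally well with neither working. If HbA1c falls in all four groups, the fall could be credited to coaching, although no randomised comparison supports that. The article says the findings will feed a larger study of the refined intervention, so the conclusion permitted here affects what is carried forward.

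**Working it through.** **1. What the randomised contrasts contain.** Let m0 be the mean HbA1c these participants would have had without coaching, and let each group's mean be m0 plus its own coaching effect: d(SW), d(SB), d(MW), d(MB), for self-selected or matched, weekly or every two weeks. The available contrasts are:

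- Selection: [d(SW) + d(SB)]/2 − [d(MW) + d(MB)]/2
- Frequency: [d(SW) + d(MW)]/2 − [d(SB) + d(MB)]/2
- Interaction: [d(SW) − d(SB)] − [d(MW) − d(MB)]

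m0 cancels from all three, and so does any effect common to the four groups. Take the 1.07-point fall that the Discussion cites for the source intervention, purely as an illustration. If all four effects are −1.07, the selection contrast is (−1.07 − 1.07)/2 − (−1.07 − 1.07)/2 = 0. If all four effects are 0, it is also 0. The other two contrasts are 0 in both cases as well. The trial cannot tell these two situations apart.

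**2. What the stated power refers to.** The Sample size section gives 19 per condition, N = 76, two-sided alpha 0.05, 80% power and a detectable f of 0.33. Using a noncentral F with noncentrality N × f² and 72 denominator degrees of freedom:

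- One factor (1 df, 38 against 38): 76 × 0.33² = 8.28, power 81.0%; f at exactly 80% power is 0.326. The stated figure reproduces.
- Four-group test (3 df): f at 80% power is 0.389, and power at f = 0.33 is 64.4%. This does not match the stated figure.

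The published figure is thus the ability to find one active level better than the other, before attrition.

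**3. How likely an uninformative tie is.** The same section mentions f = 0.1 as a small effect. Then 76 × 0.1² = 0.76, and the 1-df power is 13.8%. At that effect a non-significant contrast is expected about 86% of the time for a given factor.

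**4. What change over time could supply.** The only remaining route to a statement about each group is before-after change, the measurement-occasion term. That term mixes any coaching effect with time trend, concurrent care and possibly some regression to the mean after selection at 7.5%. The section on the introductory session has a fingerstick HbA1c taken at baseline, separate from the qualifying value. The expected fall from baseline to follow-up through selection alone is

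(r1 − r2) × SD × φ(a)/[1 − Φ(a)], with a = (7.5 − mean)/SD,

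where r1 and r2 are the correlations of the qualifying value with baseline and with follow-up. None of these inputs is in the article, so all are assumed. With r1 = r2 the fall is 0. With mean 7.0, SD 1.5, r1 = 0.85 and r2 = 0.70, it is 0.15 × 1.5 × 1.02 = 0.23 points. The range is therefore 0 to about 0.23 points, and it does not bias the randomised contrasts.

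**The case against.** Most of the article's stated purpose is comparative. The introduction speaks of the components that are most effective, the primary outcomes section names the two contrasts, the Sample size section asks for preliminary effect sizes per factor, and the closing paragraph leaves the test of effectiveness to a larger trial. The missing usual-care arm is disclosed, with reasons. On this reading, the sentence about rigor means only that the design can choose between levels in order to refine an existing intervention, and for that it is sound. This much stands. It does not rescue the promise to evaluate each group's effectiveness, or a sentence that withdraws the disclosed limitation without saying which question remains unanswered.

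Three stronger readings are tempting, and the documents do not support them:

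- **That the design can show nothing about any component.** If weekly contact beats contact every two weeks, that is a valid randomised effect of the added contact.
- **That the plan will treat the time effect as efficacy, or set it against the 1.07 figure.** No section says so. Measurement occasion belongs in a repeated-measures model, and 1.07 is cited only as the reason for choosing the intervention.
- **That selection at 7.5% builds in a large spurious fall.** That would require the qualifying value to serve as baseline, whereas the article collects a fresh one.

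**Conclusion.** The point holds for absolute effectiveness only. The randomised comparisons estimate which of two active levels is better. They cannot show that coaching, any one group or any component works against no coaching, and a tie between levels is uninformative on that question. This follows from the group definitions and needs no assumed figure. The statement in Study aims, item 1, and the last sentence of the Discussion's limitations paragraph are wrong in that sense; the Abstract's wording invites the same reading.

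The design, the sample size and the relative effects are not called into question. No numerical bias is claimed for the primary contrasts. The regression-to-the-mean range above rests wholly on assumed inputs and serves only to show why within-group change needs a label. The correction is worth making because it costs little and governs what the trial may conclude.

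**What to change.** - **Abstract (Method), Study aims item 1, and Discussion:** state the aim and the permitted conclusion as the comparative effect of two active levels of each component. Drop the wording about the effectiveness of each group and about efficacious components.
- **Discussion, last sentence of the limitations paragraph:** replace it with one on these lines: *The factorial design can identify the better of two active levels of each component; without a usual-care group it cannot show effectiveness against no coaching.*
- **Analytic plan for aim 1:** keep measurement occasion in the model. Name the between-level differences in HbA1c at the first post-intervention occasion as the effects to be reported. Label within-group change as descriptive and uncontrolled, open to time trend, concurrent care and some regression to the mean.

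The cost is wording only. No arm, visit or participant is added, and conduct is unchanged. The drawback is a slightly less favourable claim.

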## Abbreviations

T2D: Type 2 Diabetes
EBI: Evidence-Based Intervention
PHC: Peer Health Coaching
PRISM: Practical Robust Implementation and Sustainability Model
BRADD: Barren River Area Development District
